***The Intervention: Level of the FSW***

A secondary aim of this study is to determine how FSW behavioral outcomes change concordant with the fidelity of the implementation of *Mujer Segura* at each CBO and with other organizational characteristics. FSW data will be gathered at baseline (prior to counseling) and again at six-month follow-up using measures employed in our previous work with Mexican FSWs (Project #051182), which was reviewed and approved by the IRB.

Baseline and Follow-up Interview. The baseline interview (~30 min) is theory-driven and has been administered to over 1,800 FSWs in Mexico-U.S. border cities. Per the recommendations of our Mexican collaborators, all measures will be administered by computer-assisted personal interviewing (CAPI). Reading ability is not a requirement of study participation. Using CAPI technology, the interviewer will read all questions and response categories to the participant and record the participant’s responses on a computerized form.In order to measure intervention effects, the interview will be repeated with each participant at a six-month follow-up appointment. The interview covers the following domains:

 Background Characteristics. These include socio-demographics, family background variables (e.g., number of children), and financial need (e.g., number of financial dependents).

 Contextual factors. Interview questions include working conditions: work setting (e.g., street), type of sex worker (e.g., brothel-based), nature of relationship with pimp or manager (if applicable) (e.g., control over client selection), client characteristics, demands for unprotected sex, amount received for protected vs. unprotected sex, and availability of condoms and sterile syringes.

 Substance Use. History, practices and environmental influences, including age at first use of alcohol and specific drugs, amount of alcohol consumed using the AUDIT; types of substances used alone and in combination, routes of administration, and injection practices.

 Mechanisms of Change. Consistent with our theoretical framework, we include measures of attitudes, intentions, and peer norms about safer injection and sex.

 HIV and STI Knowledge will be measured with an 18-item scale that assesses awareness of the importance of condom use with respect to HIV/STI prevention (alpha = 0.75 to 0.89).

 Self-Efficacy towards Condom Use is a 5-item measure that asks participants the extent to which they are able to use a condom properly with clients, (alpha = 0.85).

 Peer norms about safer sex will be measured by two items developed by Fisher et al. (e.g., “Most people in my line of work think that I should always use condoms for vaginal intercourse” (alpha=0.96).

 Attitudes toward HIV Prevention: Four items will be used to measure attitudes toward HIV prevention (e.g., “My not having (vaginal/anal) intercourse with my clients during the next month would be: very good (5), somewhat good (4), neither good nor bad (3), somewhat bad (2), and very bad (1)” (alpha = 0.79).

 Outcome Expectancies will be measured by 6 items (alpha= 0.89. Sample items are “I believe that using condoms will protect me from getting HIV” and “I don’t think sharing my works will put me at risk for HIV”.

 Sexual Risk Behaviors include number and frequency of unprotected vaginal, oral, and anal sex with clients and with spouse or steady partner(s); number of clients (regular and non-regular); number and type of other sex partners (non-clients); number of partners who inject drugs.

Testing for HIV and STIs. A blood test will be performed at baseline and six-month follow-up to ascertain HIV serostatus. The blood draw (approximately 10 cc) and testing will take place at each participating CBO. FSWs will also receive a gynecological exam that will yield a vaginal smear and gonorrhea culture. Specimen testing will be conducted on-site at each MexFam CBO. The “Determine”® rapid HIV antibody test will be administered to determine the presence of HIV antibodies (Abbott Pharmaceuticals, Boston, MA). All reactive samples will then be tested using HIV-1 antibody by EIA and Western Blot. Syphilis serology used the rapid plasma reagin (RPR) test (Macro-Vue, Becton Dickenson, Cockeysville, MD, USA). All RPR-positive samples will be subjected to confirmatory testing using the *Treponema pallidum* hemagglutinin assay (TPHA) (Fujirebio, Wilmington, DE, USA). *Neisseria gonorrhea* and *Chlamydia trachomatis* samples will be collected by trained nurses using the Aptima® Combo 2 collection device (Genprobe, San Diego, CA), which allows for a direct target-amplified nucleic acid probe test. HIV/STI test results will be provided to participants by nurses within one week of testing. Those testing HIV-positive will be referred to the municipal health clinic in their city for free medical care. Participants who test positive for another STI will be treated on-site at the MexFam CBO.

***Data Analysis and Interpretation***

Aim 1: Equivalence testing will be used to evaluate Aim 1 using Schuirmann’s (1987) test of equivalence. A nominal alpha of .05 will be used in the proposed analysis. Given the nested data structure (i.e., service providers nested in CBOs), hierarchical linear modeling will be used to adjust standard errors for possible dependency among observations. The outcome of interest in Aim 1 focuses on *Mujer Segura* fidelity. We expect that service providers will attain approximately 90% treatment fidelity when considering that 100% is perfect fidelity.

Power calculations for equivalence tests proposed for Aim 1 were conducted using SAS® Proc Power. Using the bounds and nominal alpha specified above, along with a hypothesized difference between population group means of zero and a standard deviation of 15 in each group, the proposed sample size of 120 (10 staff x 12 CBOs) would yield power of >.89 to reject the null hypothesis of mean differences in favor of the alternative of group equivalence. This power calculation is based on the assumption that observations are independent. If the observations are dependent, this will be an overestimate of statistical power. One method of calculating power in this case is to estimate the degree to which the variance will be increased due to non-independence. Specifically, the variance will be increased by a factor of 1+(m-1)*ICC, also known as the design effect, where m is the average cluster size and ICC is the intraclass correlation coefficient. While we don’t have prior ICCs for *Mujer Segura* fidelity ratings, in our work examining service provider attitudes toward EBI implementation in CBOs, ICCs were generally low. However, in a larger and more representative study of CBOs across the U.S., the ICC was .03, and we expect the fidelity ICC to be of similar magnitude. Using the average ICC of .03 from this recent study, and an average cluster size of 8, the variance is estimated to be increased by a factor of 1.21. Given a total sample size of 96, the functional sample size would be 79.34 (i.e., total sample size/design effect), which would yield power of .80.

Aim 2: Analyses will be informed by the conceptual model proposed by [name] and adapted for this study in which implementation of EBI results in effects of organizational and provider characteristics on provider attitudes, fidelity and outcomes. Conversely, introduction of an EBI can impact organizational and—to a lesser extent—provider characteristics. In particular, we will examine changes in organizational processes (i.e., culture, climate) and group process characteristics (e.g., organizational support) as a function of *Mujer Segura* implementation. We will also examine the relationship between individual organizational factors and provider characteristics, and their impact on the implementation of *Mujer Segura*. We will then examine whether more knowledge and higher levels of perceived utility are associated with better fidelity and outcomes. In all CBOs, we will examine the degree to which Leadership and Organizational Support are associated with more positive Attitudes Toward Evidence-Based Practice, fidelity, and outcomes. We will also examine the degree to which Personal Dispositional Innovativeness and other provider characteristics such as age, education level, experience, and job tenure are associated with Attitudes Toward Evidence-Based Interventions, fidelity, and outcomes. Quantitative hypotheses to be examined include:

2a) More positive organizational culture and climate will be associated with more positive attitudes toward EBI.

2b) Personal dispositional innovativeness will mediate the relationship between staff demographics and attitudes toward EBI. Specifically, staff demographics (i.e., higher education level, shorter job tenure) will be associated with higher personal dispositional innovativeness, and personal dispositional innovativeness will be positively associated with attitudes toward EBI.

2c) Social networks indicating more connectivity and positive information regarding *Mujer Segura* will be positively associated with attitudes toward EBI.

2d) Attitudes toward EBI will meditate the relationship between personal dispositional innovativeness and implementation fidelity. Specifically, personal dispositional innovativeness will be positively associated with attitudes toward EBI, and attitudes toward EBI will be positively associated with implementation fidelity.

2e) More positive attitudes toward EBI will be associated with greater implementation fidelity.

2f) Greater fidelity will be associated with more positive FSW outcomes.

In order to examine components of relationships described in 2a-2f, analyses will use HLM in order to adjust standard errors for possible dependency among observations. Significance tests will use an alpha of .05 (two-tailed). Analyses will consist of correlations (2c, 2e, 2f), regression (2a), and tests of mediation (2b, 2d). Mediation or indirect effects will be tested using confidence intervals. Given that bootstrapping confidence intervals will likely not be an option in this study due to missing data (although missing data will be handled through multiple imputation methods [described above] for bootstrapping from a series of imputed data sets are not available), intervals will be constructed based on the distribution of the product of two random variables. This method of significance testing is superior to non-resampling alternatives in terms of having greater Type I error rate accuracy and higher power. The intervals will be estimated using PRODCLIN.

Power was calculated under the assumptions of independent and dependent observations for the proposed correlation, regression, and mediation tests. Under independence the sample size used was the total of 96 and under dependence (ICC = .03) a functional sample size of 79.34 was used (see Aim1). Power for the correlation hypotheses was evaluated using SAS® Proc Power. The power to detect a medium effect size (r = .30) for correlation hypotheses was calculated to be .85 under independence and .78 under dependence. Power for the regression hypotheses was evaluated using the Monte Carlo facility of Mplus with 20,000 replications. All parameters of the regression model were set to be medium effect sizes based on bivariate association conventions, that is, the correlation between each predictor and the outcome and the correlation among the predictors was set to be *r* = .30. The power for each regression coefficient was calculated to be .79 under independence and .71 under dependence. Finally, for tests of mediation, simulations by Fritz and Mackinnon suggest that the sample size needed for power of .80 using the proposed distribution of the product of two random variables approach (i.e., PRODCLIN) is 74, when the effect sizes for both paths are medium (i.e., ==.39). The total N of 96 used under the assumption of independence and 79.34 under dependence will be sufficient to achieve power of .80.

Aims 3 & 4: Due to potential non-independence of FSWs within CBOs, mixed linear models will be used to determine if participation in the *Mujer Segura* intervention was effective in improving sexual behavior outcomes (e.g., condom use, ratio of unprotected to protected sex) compared to the treatment-as-usual condition. Within this model, intervention condition, time, and the intervention-by-time interaction will be entered as our primary independent variables. Because participants will be nested within CBOs, this factor will be entered as a random effect. A first-order autoregressive process (a stationary AR[1] process) will be used to characterize the autocorrelation structure.

Our second set of analyses will examine efficacy of the intervention for reducing incident HIV and other STIs. We will compare intervention groups in terms of cumulative incidence and incidence density. In both cases, the numerator will be the number of women who acquire the STI in question during follow-up; for cumulative incidence, the denominator will be the total number of at-risk women, whereas for incidence density the denominator will be the total number of person years for at-risk women. For each HIV/STI outcome, Poisson regression will be used to determine if group differences are statistically significant. As an indication of effect size, we will calculate the Number Needed to Treat (NNT) for each STI outcome, where NNT represents the number of participants in the intervention who would need to be treated before one fewer person contracted the STI than would be the case had all participants received the comparison condition. Aim 4 will be addressed by using FSW behavioral outcomes described above (aim 3).

We evaluated statistical power to detect main effects and interaction effects in Hypotheses 3 and 4. Our power analyses reveal that we have an excellent chance of detecting significant main effects and interactions in our data. Hypothesis 3 uses a repeated measures design with two conditions. Assuming an attrition rate of 20%, which we achieved in *Mujer Segura*, we will have 384 subjects per group for a total of 768 subjects at the end of five years. We used findings from the parent project intervention with FSWs described in Preliminary Studies to estimate overall reductions in high-risk sex and incident STIs. We observed a 36% reduction in unprotected sex in the intervention (i.e., 18% vs. 36%), and a 40% decrease in overall STI incidence in the intervention group relative to the control (i.e., 20% vs. 38%). To estimate power in our sample, assuming a 36% reduction in unprotected sex at six-month follow-up, we calculated the following: N=384 per group, alpha = .05, and a 36% reduction in mean number of unprotected sex acts. If subjects in our experimental condition reduced the number of unprotected sex acts while the control condition did not change (i.e., group x time interaction), we would detect significant differences greater than 78% of the time. Power is slightly higher for STIs (i.e., .81). The addition of a covariate for fidelity to test hypothesis 4 does not substantially impact power estimates. Therefore, though our study is not designed to replicate findings from the parent project, we have sufficient power to detect differences between groups.

***Qualitative Analyses.*** Qualitative analyses are conceptualized as providing complementary information that will facilitate interpretation of quantitative analyses as well as provide the basis for refinement of measurement in future studies. Qualitative interviews will be recorded and transcribed, then analyzed by [name] and our two ethnographers from Ciudad Juarez. The empirical material contained in the field notes, interviews and focus group sessions will be independently coded by the project researchers to condense the data into analyzable units. Codes will also be assigned to material to reflect the social and demographic characteristics of study participants. Lists of codes developed by each qualitative researcher will be matched and integrated into a single codebook. With the final coding structure, two of our qualitative researchers will separately review transcripts to determine level of agreement in the codes applied. A level of agreement in the codes applied ranging from 66 to 97 percent depending on level of coding (general, intermediate, specific), indicates good reliability in qualitative research. The computer program QSR NVivo will then be used to generate a series of categories arranged in a treelike structure connecting text segments grouped into separate categories of codes or “nodes.” These nodes and trees will be used to further the process of axial or pattern coding to examine the association between different a priori and emergent categories.

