To avoid contamination between the experimental and comparison conditions, CBO staff will first evaluate and deliver the “usual care” counseling session to the control group before learning how to deliver the experimental counseling intervention. A total of 80 FSWs will be recruited at each site, of whom 40 will be randomly assigned to the *Mujer Segura* counseling condition and 40 will be assigned to the usual care risk-reduction counseling condition, which was developed by Mexico’s federal HIV-AIDS agency (CENSIDA) and focuses upon basic educational information, personal risk assessment, and strategies for reducing personal risk. Participants who are randomized at intake to the experimental condition will be asked to return at a later date to receive their assessment and intervention.

Phase Two: Training the CBO’s designated “internal trainer.” Once the comparison condition FSWs have been assessed and counseled, a participating CBO staff member will be designated as the CBO’s “internal trainer” and receive intensive training in both the *Mujer Segura* protocol and in effective methods for teaching the protocol to other staff. Drs. [name], [name], and [name] and two practice experts from the Ciudad Juarez training center will conduct an intensive, eight-day training.

Phase Three: The “internal trainer” trains CBO staff who in turn deliver the *Mujer Segura* intervention. The practice experts will remain at the CBO for two weeks to observe and coach the internal trainer as she trains the counselors who will deliver *Mujer Segura* to the 40 randomized FSWs, and the counselors will begin to deliver the intervention. The experts will give feedback on the delivery and help the CBO counselors resolve challenging or idiosyncratic case issues or presentations. After the practice experts leave, they will maintain weekly telephone and email contact with the CBO counselors.

While the CBO is implementing *Mujer Segura* (over approximately a six-month period), the ethnographers will return periodically to monitor intervention fidelity. Finally, at the end of implementation, the ethnographers will return to repeat the staff qualitative interviews and focus groups that were performed at the outset, in order to enable the researchers to see if any changes have occurred in staff attitudes or organizational characteristics over the course of implementing the intervention.

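### Aim 1's clustered power of .80 uses an ICC with no fidelity data behind it and too many degrees of freedom; on 12 CBOs it is about .74 even at ICC .03

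*Protocol*

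**What the plan says.** All of this is in Protocol Section 8.

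- **Test.** "Equivalence testing will be used to evaluate Aim 1", by Schuirmann's procedure, with hierarchical linear modeling for providers nested in CBOs. On the error rate: "A nominal alpha of .05 will be used in the proposed analysis".
- **Power inputs.** The calculation begins "Using the bounds and nominal alpha specified above" and assumes "a hypothesized difference between population group means of zero and a standard deviation of 15 in each group". No bound appears in the text above it or elsewhere in the protocol.
- **Independent case.** N = 120 (10 staff in each of 12 CBOs) is said to give power above .89.
- **Clustered case.** The protocol says it lacks ICCs for fidelity ratings. It reports that "in our work examining service provider attitudes toward EBI implementation in CBOs, ICCs were generally low", then turns to a larger U.S. study of CBOs in which "the ICC was .03, and we expect the fidelity ICC to be of similar magnitude". With 8 per CBO and 96 in total, the design effect is 1.21, the functional sample size 79.34 and power .80. No other ICC is tried.
- **Training model.** In Phase Three of the implementation process, practice experts "observe and coach the internal trainer as she trains the counselors who will deliver" the intervention. Each CBO has one designated internal trainer.

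**The concern.** Two features of the .80 need checking.

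First, the ICC is not a fidelity ICC for this intervention, and no reason is given for carrying it over. Fidelity here is a newly taught skill, and the counselors at a CBO learn it from the same person. That is a plausible source of within-CBO correlation which nothing in the protocol says the U.S. study shared.

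Second, dividing 96 by the design effect corrects the standard error but not the degrees of freedom. The functional sample is then used as if it were 79 independent people. Mean fidelity in a nested model is estimated from 12 CBOs.

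Fidelity and competency are the subject of Aim 1, and .80 is the only clustered power figure given for it. It leaves no margin if either input is optimistic.

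**Working it through.** **Inputs from Section 8.** SD 15; true difference 0; alpha .05, taken as .05 for each one-sided test; 12 CBOs; m = 8; N = 96; ICC .03.

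**Step 1: the protocol's functional sample size.** Design effect = 1 + (m − 1) × ICC = 1 + 7 × .03 = 1.21. Functional N = 96 / 1.21 = 79.34. Both match.

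**Step 2: the missing bound.** Equivalence is declared when |estimate| + t(.95, df) × estimated SE is below the bound Δ. With true difference 0, power is the expectation of max{0, 2Φ[(Δ − t × SE × √(U/df)) / SE] − 1}, where U is chi-square on df. Solving for the bound that gives .80 at 79.34 yields Δ of about ±5 (one-sample; exactly ±4.97). A two-group version with the functional N split in half gives about ±10 and the same power values. The round value ±5 is used below. It gives .806 at 79.34, so the stated .80 is reproduced. It also gives .890 at N = 96 and .953 at N = 120.

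**Step 3: the same standard error on CBO-based degrees of freedom.**
- Functional-N route: SE = 15 / √79.34 = 1.684.
- CBO route: variance of a CBO mean = 225 × (.03 + .97/8) = 225 × .15125 = 34.03. SE of the mean of 12 = √(34.03 / 12) = 1.684.

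The standard errors are identical, so only the degrees of freedom differ. The critical value rises from t(.95, 78) = 1.665 to t(.95, 11) = 1.796. Treating the SE as known gives a rough check, with Δ/SE = 5 / 1.684 = 2.969: 2Φ(2.969 − 1.665) − 1 = .808 on about 78 df, and 2Φ(2.969 − 1.796) − 1 = .759 on 11 df. Allowing for the estimated SE, exact integration gives .806 and **.744**. Simulation of 12 CBO means also gives .744.

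**Step 4: other ICCs.** These are assumed values, because the protocol holds no fidelity ICC. Δ = ±5, SD 15, m = 8, N = 96.

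| ICC | Design effect | Functional N | Power, protocol's method | Power, 11 df |
|---|---|---|---|---|
| .03 | 1.21 | 79.3 | .806 | .744 |
| .05 | 1.35 | 71.1 | .745 | .677 |
| .10 | 1.70 | 56.5 | .593 | .521 |
| .20 | 2.40 | 40.0 | .33 | .290 |

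**Step 5: what these ICCs mean in points.** The between-CBO SD of true mean fidelity is 15 × √ICC: 15 × √.03 = 2.6 points and 15 × √.10 = 4.7 points. A gap of about two points in that SD separates power of about .8 from about .6 by the protocol's own method.

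**The case against.** **The arithmetic at ICC .03 is exact, and the protocol discloses that it lacks a fidelity ICC.** Both are true. The fault lies in the input and the degrees of freedom, not in the division.

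**A reader might infer that the ICC is too low and the power therefore overstated on that account.** The documents do not support this as fact. They give no fidelity ICC, so that part of the loss follows only if the true value exceeds .03. Some features work the other way: outside experts coach each internal trainer for two weeks and then keep weekly contact with the counselors, and fidelity is monitored. The trainer is herself a CBO staff member, so she may be one of the eight.

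**A reader might also say that .03 is an ICC for provider attitudes.** The protocol ties attitudes only to the team's own earlier work. It does not name the outcome behind the .03. What can be said is that it is not a fidelity ICC for this intervention.

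**The back-solved bound could be wrong.** The protocol prints the power above .89 beside N = 120, not 96. A bound set to give exactly .89 at 120 (about ±4.47 one-sample, ±8.93 two-group) gives only .675 at 79.34, so it cannot be what lies behind .80. The bound used here is the one that agrees with the clustered figure under review.

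**A reader might extend the point to Aim 2, where** "Under independence the sample size used was the total of 96 and under dependence (ICC = .03) a functional sample size of 79.34 was used". This does not follow. The precision of an association between two provider-level measures depends on both ICCs, roughly 1 + (m − 1) × ICCx × ICCy. With assumed ICCs of .03 for attitudes and .10 for fidelity, that is 1 + 7 × .003 = 1.021, or an effective N of 96 / 1.021 = 94. Simulated variance inflation stayed between 0.98 and 1.04 for fidelity ICCs of .03 to .20. A higher fidelity ICC alone does not undermine the association between attitudes and fidelity.

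**Choice of degrees of freedom is usually left to the SAP.** For the analysis itself that is fair. But the protocol already states a power figure and commits to a nested model, and the figure should match that model.

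**Conclusion.** The point holds for Aim 1 only. With the bound that reproduces the stated .80, a mean over 12 CBOs tested on 11 df has power of about .74 at the protocol's own ICC. This loss needs no assumption of a higher ICC. It rests on the back-solved bound, SD 15, a true difference of zero, eight counselors in each of 12 CBOs, and alpha .05 per side.

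Separately, the ICC of .03 is unsupported for fidelity and there is no slack. If the true value were .05, .10 or .20, power would be about .75, .59 or .33 by the protocol's method, and .68, .52 or .29 on 11 df. This part is conditional, since the true ICC could also be .03 or lower.

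Nothing here shows that the design or the planned nested model is wrong, and no conclusion about Aim 2 follows.

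**What to change.** In the Aim 1 power paragraph:

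1. Print the equivalence bound, and say whether the comparison is one-sample or two-group.
2. Present .03 as an assumption, and remove the unsupported expectation that fidelity shares it.
3. Recompute power on CBO-based degrees of freedom (11 for a mean over 12 CBOs).
4. Show the result over a range of ICCs, for example .03 to .20.

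This takes a short recalculation and some rewording, with no added staff, participants or sites. The cost is that the stated power becomes less favourable: about .74 instead of .80 at ICC .03 if the back-solved bound is the one used, and lower across the rest of the range.

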2b) Personal dispositional innovativeness will mediate the relationship between staff demographics and attitudes toward EBI. Specifically, staff demographics (i.e., higher education level, shorter job tenure) will be associated with higher personal dispositional innovativeness, and personal dispositional innovativeness will be positively associated with attitudes toward EBI.

2c) Social networks indicating more connectivity and positive information regarding *Mujer Segura* will be positively associated with attitudes toward EBI.

2d) Attitudes toward EBI will meditate the relationship between personal dispositional innovativeness and implementation fidelity. Specifically, personal dispositional innovativeness will be positively associated with attitudes toward EBI, and attitudes toward EBI will be positively associated with implementation fidelity.

2e) More positive attitudes toward EBI will be associated with greater implementation fidelity.

2f) Greater fidelity will be associated with more positive FSW outcomes.

Aim 3: To determine whether the implementation of *Mujer Segura* by each CBO is associated with decreased sexual risk behaviors among Mexican FSWs over a six-month period (e.g., increased condom use with clients, reductions in STI incidence);

Hypothesis 3. As in the completed efficacy study, FSWs randomly assigned to the theory-based *Mujer Segura* intervention condition will show greater reductions in high risk sexual behavior with clients (i.e., fewer unprotected vaginal and anal sex acts, lower global STI incidence) at six-month follow-up as compared to FSWs who receive standard counseling.

Aim 4: To determine whether improvements in FSWs’ sexual risk behaviors are associated with variations in intervention fidelity and counselor competency.

Hypothesis 4. Among FSWs in the *Mujer Segura* condition, improvements in sexual behavior with clients at six-month follow-up (i.e., frequency of unprotected vaginal and anal sex, STI incidence) will be associated with higher levels of counselor competency and fidelity to the implementation model.

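### The fidelity-to-outcome question is set up twice, as a correlation powered on 96 staff (2f) and as a woman-level model without a counselor level (Hypothesis 4), and neither power statement was derived for it

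*Protocol*

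**What the plan says.** **Aim 2 (Protocol, Section 8, Data Analysis and Interpretation).** Hypothesis 2f reads "Greater fidelity will be associated with more positive FSW outcomes". The method is given as "Analyses will consist of correlations (2c, 2e, 2f), regression (2a), and tests of mediation (2b, 2d", with the general remark that "analyses will use HLM in order to adjust standard errors for possible dependency among observations". On error rate: "Significance tests will use an alpha of .05 (two-tailed". One power calculation serves all three correlation hypotheses: "The power to detect a medium effect size (r = .30) for correlation hypotheses was calculated to be .85 under independence and .78 under dependence". The sample size is 96, and the dependent case uses 79.34, carried over from Aim 1, where the design effect is for staff clustered in CBOs (ICC .03, cluster size 8).

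**Hypothesis 4 (Section 5, Specific Aims).** Among women in the Mujer Segura condition, improvements at six months "will be associated with higher levels of counselor competency and fidelity to the implementation model".

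**Aims 3 & 4 (Section 8).** The analysis is described in one sentence: "Aim 4 will be addressed by using FSW behavioral outcomes described above (aim 3". The Aim 3 model is a mixed linear model on individual women. It has condition, time and their interaction as fixed effects, CBO as the random effect, and an AR(1) structure over time. No counselor level is named. The power text for Hypothesis 4 says only that a fidelity covariate makes no substantial difference to the Aim 3 power.

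**The concern.** Hypothesis 2f and the fidelity part of Hypothesis 4 ask essentially the same thing: do women do better when the intervention is delivered with higher fidelity? One version takes its sample size from staff, the other from women. The protocol does not say how they relate or which one stands.

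The power attached to 2f is the calculation used for 2c and 2e, which relate staff measures to each other. The outcome in 2f is measured on women, and each counselor has few of them. If that figure is taken at face value, a null 2f could be read as well-powered evidence that fidelity does not matter. That bears on Aims 2 and 4.

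The Hypothesis 4 version has its own gap. Its power is borrowed from a comparison between arms with 384 women per group, whereas the fidelity question is asked within one arm. Its model also ignores that women share a counselor.

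**Working it through.** **Inputs from the protocol.** Eight staff per CBO to be trained as counselors (Section 7) in 12 CBOs: 8 × 12 = 96. Women randomized to Mujer Segura: 40 per CBO (Section 8), 40 × 12 = 480. Attrition 20%: 480 × 0.8 = 384 followed up. Alpha .05, two-sided. r = .30.

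**Inputs assumed.** Even caseloads, so 480/96 = 5 women enrolled and 384/96 = 4 followed up per counselor. The counselor ICC of the women's outcome is not in the protocol; its .03 is for staff within CBOs. I use .03, .05, .10 and .20.

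**1. Reproduce the stated power.** Design effect 1 + (8 − 1) × .03 = 1.21, and 96/1.21 = 79.34. Fisher z with standard error 1/√(N − 3) gives .847 at N = 96 and .772 at N = 79.34. With the small bias term it gives .851 and .777. The stated .85 and .78 reproduce.

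**2. Power for 2f if .30 is the correlation with a counselor's true mean outcome.** The staff count of 96 implies one outcome score per counselor, here a mean of k = 4 women.

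- Reliability = 4 × ICC / (1 + 3 × ICC)
- Observable r = .30 × √reliability
- Power from the Fisher z calculation in step 1, with the bias term and a t-based critical value

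| Counselor ICC | Reliability | Observable r | Power, N = 96 | Power, N = 79.34 | True r needed to observe .30 |
|---|---|---|---|---|---|
| .03 | .11 | .10 | .16 | .14 | .90 |
| .05 | .17 | .13 | .23 | .20 | .72 |
| .10 | .31 | .17 | .37 | .31 | .54 |
| .20 | .50 | .21 | .55 | .47 | .42 |

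A simulation at N = 96 (20,000 replicates) gave .16, .24, .37 and .56.

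**3. Power of the same test on women.** With a counselor-level fidelity score, the woman-level correlation is .30 × √ICC and the effective sample size is 384/(1 + 3 × ICC).

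| Counselor ICC | Woman-level r | Effective N | Power |
|---|---|---|---|
| .03 | .052 | 352 | .16 |
| .05 | .067 | 334 | .23 |
| .10 | .095 | 295 | .37 |
| .20 | .134 | 240 | .55 |

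These match the N = 96 column in step 2. The loss comes from having few women per counselor, not from choosing a staff-level correlation.

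**4. Type I error of the CBO-only model.** If fidelity is one score per counselor and counselor variance is left in the residual, the variance of the fidelity slope is understated by 1 + 3 × ICC. The true two-sided error is P(|Z| > 1.96/√(1 + 3 × ICC)).

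| Counselor ICC | 1 + 3 × ICC | Effective cut-off | True type I error |
|---|---|---|---|
| .03 | 1.09 | 1.88 | .06 |
| .05 | 1.15 | 1.83 | .07 |
| .10 | 1.30 | 1.72 | .09 |
| .20 | 1.60 | 1.55 | .12 |

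**The case against.** The strongest reply is that the stated power is not wrong. It reproduces, and it is correct if r = .30 means the correlation between the variables as analysed. That stands, so this is not a calculation error. What remains is that the protocol supports .30 for 2f only by calling it a medium effect. With 4 women per counselor, an observed .30 requires a true correlation of .90 to .42 over the ICC range in the working.

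A second reply is that no averaging over women is described, and that hierarchical models are named for all of 2a to 2f. This also stands: the staff-level unit is inferred from the sample size of 96. It does not rescue the figure. If the unit is staff, each counselor needs a score built from her women; if the unit is women, 96 is not the sample size.

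Third, the size of the loss depends on an ICC and a caseload that the protocol does not give. At an ICC of .50 power would be .76/.68. The loss can only be shown as a range. Likewise, the type I error figures assume one fidelity score per counselor; scores that vary from session to session would inflate it less.

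Fourth, Section 8 calls relating the women's outcomes to fidelity a secondary aim, and precedence between overlapping secondary analyses could be left to a statistical analysis plan. That limits the weight of the point. But the protocol itself fixes both versions and attaches a power statement to each.

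A reader might also infer that the two analyses could give opposite answers, or that they concern different outcomes and different women. The text does not show this. Attenuation pushes a result toward null, not toward reversal. The outcomes in 2f are undefined, and its population is most naturally the Mujer Segura arm. Nor is Hypothesis 4 identical to 2f, since it also covers competency.

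**Conclusion.** The point holds in a limited form. The protocol sets up essentially one question as two analyses with different implied units and does not reconcile them. The .85/.78 is arithmetically sound for an observed correlation of .30 but was not derived for 2f's data.

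If .30 is the correlation with a counselor's true mean outcome, power at N = 96 / 79.34 is about .16/.14, .23/.20, .37/.31 or .55/.47 at an assumed counselor ICC of .03, .05, .10 or .20, with even caseloads of 4. It would be tempting to conclude that 2f is shown to be underpowered, or that moving to women restores the power. Neither follows: the first rests on assumed inputs, and the woman-level model gives the same figures.

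The case for a single woman-level model is that it gives one coherent test and, with a counselor random effect, a valid standard error. The CBO-only model, with fidelity scored per counselor, has a true type I error of about .06, .07, .09 or .12 at those ICCs. The statement that a fidelity covariate barely affects power is unsupported for the same reason as the .85/.78: neither allows for clustering of women by counselor.

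**What to change.** - State that 2f and the fidelity part of Hypothesis 4 are one hypothesis, tested once among women in the Mujer Segura arm. The model is six-month outcome on the counselor's fidelity score, adjusted for the woman's baseline value, with counselor and CBO as random effects.
- Keep competency as a separate part of Hypothesis 4.
- Remove 2f from the list of correlations and from the .85/.78 statement, which can stay for 2c and 2e.
- Replace the .85/.78 for 2f, and the Aims 3 & 4 statement that a fidelity covariate does not materially change power, with power over a stated range of counselor ICCs.

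The cost is wording, a short calculation and a counselor ID on each woman's record. The downside is a less favourable power figure. Baseline adjustment may recover some precision, but the protocol gives no figure from which to say how much.
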